#### CFS

CFS will be assessed under a slit-lamp microscope with blue light and a yellow band–pass filer according to the van Bijsterveld grading system, in which the ocular surface will be divided into 3 zones: the nasal bulbar conjunctiva, temporal bulbar conjunctiva, and cornea [46]. Each zone will be evaluated on a scale from 0 to 3, with 0 indicating no staining and 3 indicating confluent staining. The maximum potential score is 9.

#### Schirmer Test I for Tear Secretion Volume

Schirmer test I will be performed without topical anesthesia after all other examinations. A Schirmer test strip will be placed on the outer one-third of the temporal lower conjunctival fornix for 5 minutes. The length of the moisture stain on the filter paper (in mm) will be recorded [47].

#### Environmental Conditions

The temperature of the examination room will be set at 26 °C in summer and at 24 °C in winter, with a constant relative humidity of 50%, following *Guidelines for Design and Operation of Hospital HVAC Systems*, established by the Healthcare Engineering Association of Japan [48].

### Primary Outcome

The primary outcome will be the sensitivity and specificity of the *test method* for DED diagnosis, compared with the *standard method*. Sensitivity and specificity will be calculated based on the diagnostic results of the 2 methods. In the *test method*, an app-based J-OSDI total score ≥13 measured using the DEA01 and an MBI score greater than the cutoff value based on the secondary outcome (5) will be considered DED positive. In the *standard method*, a paper-based J-OSDI total score ≥13 and TFBUT ≤5.0 seconds will be considered DED positive.

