Recent studies have suggested the maximum blink interval (MBI) measurement as a noninvasive alternative to TFBUT, with the MBI defined as the maximum length of time a patient is able to keep their eyes open between 2 blinks [26]. A positive correlation has been reported between the MBI and TFBUT, likely owing to the MBI’s capability to reflect ocular surface integrity [26-30]. The simplicity and noninvasive nature of MBI measurements underscores its candidacy as an alternative to TFBUT for screening purposes. Our earlier studies have indicated that the concomitant use of the MBI and the Ocular Surface Disease Index (OSDI) questionnaire can determine DED with similar accuracy to standard diagnostic methods using TFBUT and the OSDI [31,32].

Mobile health (mHealth) is defined by the World Health Organization as “medical and public health practice supported by mobile devices, such as mobile phones, patient monitoring devices, personal digital assistants (PDAs), and other wireless devices” [33]. The capability of mHealth to digitally perform therapeutic activities has raised the interest of clinicians and providers due to its potential use in disease prevention, diagnosis, and treatment through commonplace smart devices [32,34-39]. Previous studies concerning the validity and reliability of smartphone-based administration of MBI examinations and OSDI questionnaires yielded a satisfactory result [3,32,40]. Reported findings suggest that noninvasive and nonintrusive DED screening during activities of daily living may be possible, enabling an earlier DED diagnosis and interventions in remote settings [40,41]. More importantly, this possibility may have implications in accurately identifying undiagnosed patients with DED, allowing for timely intervention, preventing a further decrease in QoL, and reducing societal economic loss.

In this clinical study, we intend to use an in-house smartphone app, namely, the DEA01, which has been designed as an investigational device to facilitate a DED diagnosis. This study will aim to evaluate the capabilities of the DEA01 in facilitating a diagnosis of DED.

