### Study Procedures

After enrollment in the study, patients will be evaluated for DED by clinical research coordinators using the DEA01. A physician will diagnose DED using the *standard method* without checking *test method* results. Details regarding the *test method* and *standard method* are shown in Textbox 2.

*Test* and *standard method.*
**
*Test method*
**
Dry eye disease (DED) diagnosis based on the app-based Japanese version of the Ocular Surface Disease Index (J-OSDI) and maximum blink interval (MBI), using the DEA01Patients will respond to the app-based J-OSDI questionnaire and be measured using the app-based MBI on the DEA01. The J-OSDI questionnaire is used to evaluate the subjective symptoms of DED on a 100-point scale [43,44]. The MBI will be defined as the length of time that a patient can keep their eyes open before blinking [26]. The app-based MBI will be measured using the smartphone’s camera on the DEA01 and a visually confirmed MBI will be measured using a stopwatch.
**
*Standard method*
**
DED diagnosis using a paper-based J-OSDI and tear film breakup time (TFBUT)Patients will respond to the paper-based J-OSDI questionnaire and be measured using TFBUT [20]. The diagnosis of DED using the *standard method* will be based on 2016 Asian Dry Eye Society criteria, with positive subjective symptoms (J-OSDI total score ≥13) and decreased TFBUT (≤5.0 s) being used to diagnose DED [20]. Based on the diagnosis using the *standard method*, patients will be allocated to DED and non-DED groups.

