#### MBI

The MBI is defined as the length of time that a patient is able to keep their eyes open before blinking during each trial [26]. In the *test method*, the app-based MBI will be measured using the smartphone’s camera on the DEA01, and visually confirmed MBI will be measured using a stopwatch by a trained clinical research coordinator. In the *standard method*, the MBI will be measured by a physician using a slit-lamp microscope. In both methods, the MBI will be measured twice for each patient and the average value will be adopted as the result. An MBI exceeding 30 seconds will be recorded as 30 seconds. The MBI cutoff value will be calculated using receiver operating characteristic (ROC) curve analysis [31].

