The DEA01 is used to help assess subjective symptoms and collect objective findings through OSDI administration and MBI measurements, respectively. The reliability and validity of the MBI and OSDI in a remote setting to facilitate DED diagnosis have been previously shown through a previous DEA01 app designed for DED research, namely, DryEyeRhythm [31,32]. Additionally, discrepancies between results obtained from the standard paper-based OSDI and app-based OSDI have been previously shown to be acceptable [32]. Our prior study utilized the MBI cutoff derived from a slit-lamp microscopy–based MBI study [26]. This study aims to establish an MBI cutoff for smartphone app-based diagnosis assistance for DED. The establishment of an optimal MBI cutoff value will enable more robust and reliable app-based remote DED diagnosis assistance through the use of the DEA01.

In this study, the diagnostic performance utilizing the app-based MBI as a proxy for the standard TFBUT will be evaluated using the DEA01. TFBUT reflects tear film stability and homeostasis, acting as a critical component of DED diagnosis. However, it requires specialized tools and materials, including fluorescein dye and slit-lamp microscopy. Moreover, the invasive nature of the examination disrupts the in vivo status of the tear film and the ocular surface [20-23]. Some studies have shown that fluorescein dye results are not consistently reproducible and that the dye may negatively affect the stability of the tear film [57-59]. The MBI has been shown to have a positive correlation with TFBUT [26], suggesting that the MBI can be used as a noninvasive, nonintrusive metric to substitute for TFBUT. An online screening test, based on a patient’s self-measurement of the time from stopping blinking to feeling discomfort, has shown the utility of screening for DED detection [26,60]. However, the DEA01 may be more objective as it automatically measures the MBI using the sensors of a smartphone camera and allows for the evaluation of DED symptoms using the J-OSDI questionnaire. This study seeks to assess the viability of replacing TFBUT with app-based MBI measurements, which may enable remote, noninvasive, and nonintrusive diagnosis assistance concerning DED.

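### The primary-outcome rule calls patients DED positive when MBI is above the cutoff, the opposite of the direction the protocol's own rationale implies

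*Protocol article*

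**What the plan says.** Protocol article, Primary Outcome: the test method is positive when the app J-OSDI total is 13 or more and "an MBI score greater than the cutoff value based on the secondary outcome (5) will be considered DED positive". The next sentence gives the reference rule: "a paper-based J-OSDI total score ≥13 and TFBUT ≤5.0 seconds will be considered DED positive". Study Procedures (Textbox 2) says the same of the reference, with "decreased TFBUT (≤5.0 s) being used to diagnose DED", and the TFBUT section repeats the 5.0 s cutoff.

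On how the two time measures relate, the Introduction states: "A positive correlation has been reported between the MBI and TFBUT, likely owing to the MBI’s capability to reflect ocular surface integrity". The Discussion states: "The MBI has been shown to have a positive correlation with TFBUT [26], suggesting that the MBI can be used as a noninvasive, nonintrusive metric", and presents that metric as a replacement for TFBUT. The MBI section fixes the scale: "The MBI is defined as the length of time that a patient is able to keep their eyes open before blinking during each trial". Values are in seconds, averaged over two trials and capped at 30 s. No inverted or rescaled MBI score is described.

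The cutoff comes from an ROC analysis (MBI; Secondary Outcomes, item 5; Sample Size and Statistical Analyses). None of those sections says whether low or high MBI counts as positive.

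**The concern.** If MBI rises with TFBUT, and DED requires a low TFBUT, then DED should go with a short MBI. The rule in Primary Outcome instead counts the longer MBI as the sign of disease. A symptomatic patient who reaches the 30 s ceiling would be test-positive at any cutoff below 30 s.

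This is the positivity rule of the primary endpoint. Under Sample Size and Statistical Analyses, the concordance rate, predictive values and likelihood ratios come from the same cross-classification, so they inherit the error. The Discussion also names establishing an app-based MBI cutoff as an aim. A cutoff published with the wrong direction could not be used correctly.

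**Working it through.** **Direction, from the text**

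1. DED on the reference requires TFBUT ≤5.0 s (Study Procedures, TFBUT, Primary Outcome): low value = disease.
2. MBI and TFBUT are positively correlated (Introduction, Discussion).
3. MBI is the time the eyes stay open, in seconds (MBI section), so its scale is not reversed.
4. Steps 1 to 3 imply low MBI = disease. Primary Outcome has high MBI = disease. The ROC text gives no direction, so nothing overrides it.

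**The plan's own figure**

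The only related number is the sample size. The formula is not shown. Assuming the usual precision formula with p = 0.5, n = 1.96² × 0.5 × 0.5 / 0.10² = 96.04, so 97, close to the stated 100 per group. MBI direction does not enter this, so the sample size stands.

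**Effect at a fixed cutoff, without assumptions**

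Let A be app J-OSDI ≥13 and c the cutoff. MBI ≤ c and MBI > c are complements, so among DED patients

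Se(A alone) = Se(A and MBI ≤ c) + Se(A and MBI > c).

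The false-positive rates among non-DED patients add in the same way. Subtracting, with J = Se + Sp − 1:

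J(as written) = J(A alone) − J(low-MBI rule).

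Two consequences follow. If the low-MBI rule has any positive J, the written rule is worse than the questionnaire alone. If the low-MBI rule beats the questionnaire alone, the written rule has a negative J.

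**Worked example (assumed inputs)**

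Take P(A) = 0.95 in DED and 0.50 in non-DED, and let MBI in the low = positive direction have accuracy 0.70/0.70 among symptom-positive patients.

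- Low-MBI rule: Se = 0.95 × 0.70 = 0.665; Sp = 1 − 0.50 × 0.30 = 0.85; J = 0.515.
- As written: Se = 0.95 × 0.30 = 0.285; Sp = 1 − 0.50 × 0.70 = 0.65; J = −0.065.
- Check: 0.515 − 0.065 = 0.45 = 0.95 − 0.50, the J of the questionnaire alone.

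**Simulation (assumed inputs)**

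The simulation used 400,000 patients, TFBUT ≤5 s in 50%, paper J-OSDI ≥13 in 70%, J-OSDI unrelated to either time measure, and MBI with a median of 12 s capped at 30 s. The cutoff was the Youden optimum for low MBI = positive.

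| Correlation MBI-TFBUT | Low-MBI rule Se / Sp | J | As written Se / Sp | J | Sum of J |
|---|---|---|---|---|---|
| 0.2 | 0.503 / 0.766 | +0.269 | 0.433 / 0.672 | +0.105 | 0.374 |
| 0.5 | 0.612 / 0.810 | +0.422 | 0.323 / 0.629 | −0.048 | 0.374 |
| 0.7 | 0.695 / 0.846 | +0.541 | 0.242 / 0.592 | −0.166 | 0.375 |

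The constant sum is J for app J-OSDI alone, as the identity requires. With a correlation of −0.2 between J-OSDI and both time measures, the J values are +0.319 and +0.085, +0.440 and −0.035, and +0.562 and −0.158.

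**If the ROC were also built with high MBI = positive**

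The rows above apply a cutoff found in one direction to a rule in the other. If the reversed direction is used throughout, the AUC of MBI in the table's three scenarios is 0.429, 0.325 and 0.255. The curve lies below the diagonal and the optimum moves toward an end of the scale. At the low end every patient passes the MBI criterion and the rule becomes app J-OSDI alone. From the 0.5 row, that is Se = 0.612 + 0.323 = 0.935 and Sp = 0.810 + 0.629 − 1 = 0.439.

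**The case against.** The best defence is that this is a one-word slip in a condensed article. The approved protocol (V.1.1.1, cited under Ethics Approval) is not shown and may have it right. An ROC curve below the diagonal would expose the slip, and because MBI is stored as a time, the table could be recomputed. All of that may be true. However, condensing explains omissions, not a reversed inequality. Finding the cutoff is also a separate step from classifying patients, and the classification rule is what Primary Outcome fixes. An analyst must either follow it and misclassify, or depart from it without a documented basis.

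Three limits stand:

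- The low-MBI direction is implied by the stated correlation and the TFBUT rule. The article never states it as a rule, and gives no comparison of MBI in DED and non-DED patients.
- A reader might infer that the primary results would be meaningless, or no better than chance. The documents do not support that. They give no MBI-TFBUT correlation, and over the assumed range the written rule runs from some remaining discrimination (J about +0.11, carried by J-OSDI) to worse than chance (about −0.17). The result also depends on which direction was used to choose the cutoff.
- A reader might apply low MBI = positive directly to secondary outcome 4. That outcome is the ROC of the test method, which also includes J-OSDI, so the direction applies only to its MBI component.

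**Conclusion.** Wrong as written. The inequality in Primary Outcome contradicts the direction implied by the Introduction, Study Procedures, TFBUT and Discussion sections, and no other text corrects it. Applied literally, the MBI component works against detection, so the primary sensitivity and specificity, and the concordance, predictive values and likelihood ratios, are invalid for the intended test. The identity behind this holds at any fixed cutoff. The size is illustrative only: a drop in Youden index of about 0.16, 0.47 and 0.71 at assumed correlations of 0.2, 0.5 and 0.7, with the cutoff chosen for low MBI = positive. The contradiction itself rests on no assumed number.

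**What to change.** Reconcile Primary Outcome with the Introduction, Study Procedures and Discussion by reversing the inequality: test-positive is app J-OSDI ≥13 together with an app-based MBI at or below the cutoff. State explicitly how a value equal to the cutoff is classified, since the article is silent on ties. Give the same direction for the ROC analyses of MBI itself (secondary outcomes 5 to 7) and for the MBI component of outcome 4.

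The cost is a short documented amendment or correction. It is not quite nothing: the protocol has review-board approval, and enrolment was planned from February 1, 2023, before the article appeared on March 13, 2023. The sample size does not change, and no data are lost because MBI is recorded as a time.

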### Secondary Outcomes

Secondary outcomes are as follows:

An overall concordance rate between the *test method* and *standard method*A positive/negative predictive value between the *test method* and *standard method*A positive/negative likelihood ratio between the *test method* and *standard method*An area under the ROC curve of the *test method* for DED diagnosis using the *standard method*An MBI cutoff value of the *test method* for DED diagnosis using the *standard method*An area under the ROC curve of the *test method* for TFBUT ≤5.0 secondsAn MBI cutoff value of the *test method* for TFBUT ≤5.0 secondsInternal consistency of the app-based J-OSDICorrelation, agreement, and comparison between the app-based J-OSDI and paper- based J-OSDICorrelation, agreement, and comparison between the app-based MBI and slit lamp– based MBICorrelation and comparison between TFBUT and the app-based MBICorrelation and comparison between TFBUT and slit lamp–based MBIDEA01 operability and usabilityDEA01 failureAdverse events

Secondary outcomes 1 to 4 were set to evaluate the DED diagnosis accuracy of the *test method* compared with that of the *standard method*. Secondary outcome 5 was included to determine the cutoff value for the app-based MBI using ROC analysis for DED diagnosis. Secondary outcomes 6 and 7 were included to determine if MBI measurements could be used as a substitute for TFBUT measurements. Secondary outcomes 8 and 9 were set to evaluate the reliability and validity of the app-based J-OSDI. Secondary outcomes 10 to 12 were set to evaluate the validity of app-based and slit lamp–based MBIs. In secondary outcome 13, patients will answer the following questions: “I think it’s easy to operate this smartphone app,” “I can use this smartphone app by myself,” “I want to be tested using this smartphone app rather than being tested at a medical institution,” and “I will continue to use this smartphone app” [49,50]. Patients will answer these questions on a 5-point Likert scale (1, strongly disagree; 2, disagree; 3, neutral; 4, agree; and 5, strongly agree) [51]. Secondary outcomes 14 and 15 were set to evaluate the safety and stability of the DEA01. DEA01 failure is defined as something not working as expected. Adverse events comprise unexpected signs, symptoms, or diseases encountered during the clinical trial, regardless of whether they are related to treatment. If serious adverse events or failure occur, these will be referred to the Juntendo Hospital Certified Review Board, and appropriate treatments will be provided as needed.

### Sample Size and Statistical Analyses

In total, the enrollment of a minimum number of 220 study patients will be required. The CI for the sensitivity and specificity of the *test method* is set at ±10%. It is possible to calculate a sample size and a CI (a margin of error) using the following formula [52]:

**(2)**

Therefore, the minimum sample size will be 100 patients in each group. To meet the minimum required number of patients in each group, the target total number of patients will be set at 110 for each group, assuming a 10% exclusion rate due to missing data.

For the primary end points, the sensitivity and specificity of DED diagnosis using the DEA01 will be calculated using ROC curve analysis with the cutoff value for the app-based MBI in the *test method*. This cutoff value will be calculated using ROC curve analysis [31]. The ROC curve will show sensitivity (positive rate) on the vertical axis and 1-specificity (false positive rate) on the horizontal axis, and the plots will be connected using straight lines. The point at which the sensitivity and specificity for DED diagnosis using the app-based MBI will be maximized and will be set as the cutoff value for MBI [31].

The secondary outcomes of the overall concordance rate, positive/negative predictive value, and positive/negative likelihood ratio will be calculated by comparing the DED diagnosis results from the *test method* with the results from *standard method* in a mixed matrix. The diagnostic performance of DEA01 will be evaluated through calculating the area under the ROC curve plotted from the sensitivity and specificity of the *test method*. The substitutability of MBI measurement for TFBUT measurement in DED diagnosis will be assessed using ROC curve analysis and through calculating the area under the ROC curve, using the cutoff value of the app-based MBI for TFBUT ≤5 seconds. The internal consistency of the app-based J-OSDI will be evaluated using factor analysis and Cronbach α coefficient, with α>0.70 considered an acceptable range [53]. Correlation and consistency will be evaluated using Pearson or Spearman correlation coefficients, an intraclass correlation coefficient, and Bland-Altman analysis. In each patient group, study patients’ backgrounds will be analyzed using a 2-tailed unpaired *t* test for continuous variables and a chi-square test for categorical variables. If a continuous variable does not clearly follow a normal distribution, it will be appropriately transformed to a logarithm and aggregated with the mean and SD or the median and IQR will be used as descriptive statistics. The operability and usability of the DEA01 will be evaluated in each group using the average score of the 5-point Likert scale responses to the operability and usability questions and the number of patients who answered better or worse than neutral using 2-tailed unpaired *t* and chi-square tests. For safety assessment, the frequency and rate of adverse events will be calculated for each group, and between-group comparisons will be performed using Fisher exact probability or chi-square tests.

A 2-sided level of significance will be set at 5%, and the confidence coefficient will be set at 95%, unless otherwise specified. Missing value completion will not be performed.

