**Methods:**

In this multicenter, open-label, prospective, and cross-sectional study, the *test method* will involve using the DEA01 smartphone app to collect and evaluate DED symptoms, based on the Japanese version of the Ocular Surface Disease Index (J-OSDI), and to measure the maximum blink interval (MBI). The *standard method* will then involve a paper-based J-OSDI evaluation of subjective symptoms of DED and tear film breakup time (TFBUT) measurement in an in-person encounter. We will allocate 220 patients to DED and non-DED groups, based on the *standard method*. The primary outcome will be the sensitivity and specificity of the DED diagnosis according to the *test method*. Secondary outcomes will be the validity and reliability of the *test method*. The concordance rate, positive and negative predictive values, and the likelihood ratio between the *test* and *standard methods* will be assessed. The area under the curve of the *test method* will be evaluated using a receiver operating characteristic curve. The internal consistency of the app-based J-OSDI and the correlation between the app-based J-OSDI and paper-based J-OSDI will be assessed. A DED diagnosis cutoff value for the app-based MBI will be determined using a receiver operating characteristic curve. The app-based MBI will be assessed to determine a correlation between a slit lamp–based MBI and TFBUT. Adverse events and DEA01 failure data will be collected. Operability and usability will be assessed using a 5-point Likert scale questionnaire.

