### Study Design

In this multicenter, open-label, prospective, and cross-sectional study, patients will be evaluated for DED using the DEA01 (*test method*). A physician will then provide a DED diagnosis based on 2016 Asia Dry Eye Society criteria [20] (*standard method*). To ensure that the *test method* will not affect a patient’s treatment plan, the physician will make a diagnosis using only *standard method* results without reviewing *test method* results. A minimum number of 220 patients will be enrolled, with patients allocated into a DED group or a non-DED group based on the diagnosis obtained using the *standard method*. The study design is shown in Figure 2.

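### Enrolling 220 does not by itself secure 100 evaluable patients per group or ±10-point precision for both primary measures, because diagnosis after enrolment decides the split

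*Protocol article*

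**What the plan says.** Under Sample Size and Statistical Analyses, the article sets the confidence interval for sensitivity and for specificity at ±10% and, from a formula not reproduced in the text at hand, concludes that "the minimum sample size will be 100 patients in each group". It then adds an allowance for losses: "the target total number of patients will be set at 110 for each group, assuming a 10% exclusion rate due to missing data". The total follows: "In total, the enrollment of a minimum number of 220 study patients will be required". The same section says that "the confidence coefficient will be set at 95" per cent and that "Missing value completion will not be performed", so patients with missing data drop out of the analysis.

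Study Design describes how the groups arise: "A minimum number of 220 patients will be enrolled, with patients allocated into a DED group or a non-DED group", according to the standard-method diagnosis. Textbox 2 gives that diagnosis: a paper J-OSDI score of at least 13 together with a tear film breakup time of 5.0 seconds or less. Textbox 1 admits patients with known or suspected DED. The Methods paragraph of the abstract gives the total without calling it a minimum: "We will allocate 220 patients to DED and non-DED groups". The Results section expects enrolment to run from February 1 to July 31, 2023.

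**The concern.** The article states three things that fit together only under a condition it does not mention: a requirement per group, a total, and a recruitment scheme that does not fix group sizes. Sensitivity is estimated only in patients with DED and specificity only in those without, so each has the precision of its own group and not of the total. If one group is much smaller, one half of the primary outcome is estimated less precisely than the article promises. The total of 220 also falls slightly short on its own terms once the assumed 10% is lost.

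**Working it through.** **Inputs from the article.** 100 required per group; 110 targeted per group; 220 in total; 10% excluded; half-width 10 points; 95% confidence; no imputation.

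**Assumptions.** The formula is not visible, so I use the usual one for a single proportion, n = z²p(1−p)/d². The DED share among enrolled patients is not given, so I show a range. The Introduction's prevalence of 5% to 50% is general background and does not describe this clinic population.

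**1. Reproducing the 100.** With d = 0.10 and p = 0.5:
- z = 1.96: 3.8416 × 0.25 / 0.01 = 96.04, so 97.
- z = 2: 4 × 0.25 / 0.01 = 100.

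The figure of 100 is therefore reproduced with z = 2, or is a rounding up of 97.

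**2. The inflation.**
- As stated: 100 × 1.10 = 110. After a 10% loss, 110 × 0.90 = 99 per group and 220 × 0.90 = 198 in total, against 200 required.
- Consistent with a 10% loss: 100 / 0.90 = 111.1, so 112 per group and 224 in total.
- Effect on precision: 1.96 × √(0.25/99) = 0.098, or ±9.8 points. The target is still met.

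**3. The split.** With 198 evaluable patients, the smaller group has n = 198 × (1 − larger share), and its half-width is 1.96 × √(p(1−p)/n).

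| Larger : smaller group | Evaluable in smaller group | Half-width at p = 0.5 | Half-width at p = 0.8 |
|---|---|---|---|
| 50 : 50 | 99 | 9.8 | 7.9 |
| 60 : 40 | 79 | 11.0 | 8.8 |
| 70 : 30 | 59 | 12.7 | 10.2 |
| 80 : 20 | 40 | 15.6 | 12.5 |

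Half-widths are in percentage points. The table is symmetric: if DED is the minority, the loss falls on sensitivity; if it is the majority, on specificity.

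**4. Where ±10 is lost.**
- At p = 0.5 the smaller group needs 96.04 patients. 96.04/198 = 48.5%, so the limit is passed once the larger group exceeds about 51.5%.
- At p = 0.8 it needs 3.8416 × 0.16 / 0.01 = 61.5 patients. 61.5/198 = 31.0%, so the limit is about 69%.

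**5. Chance of filling both groups at exactly 220.** Let each patient have DED with a fixed probability and be evaluable with probability 0.9, independently. Exact binomial sums give these probabilities:

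| DED share | Both groups ≥ 100 | Both groups ≥ 97 |
|---|---|---|
| 50% | 7.1% | 28.2% |
| 60% | 0.13% | 0.73% |

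With 224 enrolled and a 50% share, the chance that both reach 100 is 18.2%. Correcting the inflation alone therefore does not settle the matter.

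**The case against.** The strongest reply is that 220 is a floor. Study Design and the sample size section both call it a minimum, and the target of 110 is set per group. All examinations take place within one day, so group counts could be followed during recruitment and enrolment continued until both groups are full. This stands as far as it goes: a reader might infer that the study cannot reach 100 per group, and the text does not support that. But permission to exceed 220 is not a rule for doing so. The article links neither the minimum nor the per-group target to what happens when the split is unequal, and it gives an enrolment end date. The full protocol may hold such a rule, so the point is limited to what the article states: a precision figure without its condition.

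It can also be said that 100 is more than ±10 points requires and that p = 0.5 is the worst case. Both are true. With 97 per group the target is met at any true value, and at 0.8 about 62 patients suffice, so a 60:40 split would do no harm there. This is why both columns belong in the plan.

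Two further inferences are tempting and go too far. One is that both groups can never reach 100 after exclusions; that holds only if exactly 10% are lost, and with random losses the chance at a 50% share is 7.1%. The other is that the non-DED group will be the smaller one. Recruiting known or suspected cases makes that plausible, but a DED diagnosis needs both criteria, a patient who fails either counts as non-DED, and the article gives no figure for the share.

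**Conclusion.** The point holds in a conditional form. The inflation slip is minor: one evaluable patient per group, with ±9.8 points still achieved at an equal split. The substantive defect is that ±10 points is stated without condition for both measures, although it depends on a near-equal split that the article neither assumes openly nor supports with an expected share. With 198 evaluable patients, the smaller group misses ±10 points once the larger share passes about 51.5% (true value 0.5) or about 69% (true value 0.8), reaching 15.6 or 12.5 points at 80:20. These figures rest on an assumed range of splits, the usual normal-approximation interval, and an enrolment of 220 with 10% lost. They do not show that the study will fall short, nor which of the two measures would suffer.

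**What to change.** - Correct the inflation to 112 per group (224 in total), or keep 110 and state that about 99 evaluable patients per group are expected.
- Replace the unconditional ±10% with the expected half-widths for sensitivity and specificity across a range of splits, for example 50:50 to 80:20, at true values of 0.5 and 0.8, as in the table above.
- If ±10 points is wanted for both measures whatever the split, say so and count evaluable patients in each diagnosis group instead of the overall total.

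The first two changes cost a restated figure and at most four more patients; the price is that the stated precision for the smaller group looks less favourable. The third could be expensive. The enrolment at which 100 evaluable patients are expected in the smaller group is 100 / (0.90 × smaller share): 278 at 60:40, 371 at 70:30 and 556 at 80:20. It is therefore the sponsor's choice and not needed to make the text correct.
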